## Abstract

**Background:**

Transplantation is the only treatment offering long-term benefit to patients with chronic kidney failure. Live donor nephrectomy is performed on healthy individuals who do not receive direct therapeutic benefit of the procedure themselves. In order to guarantee the donor's safety, it is important to optimise the surgical approach. Recently we demonstrated the benefit of laparoscopic nephrectomy experienced by the donor. However, this method is characterised by higher in hospital costs, longer operating times and it requires a well-trained surgeon. The hand-assisted retroperitoneoscopic technique may be an alternative to a complete laparoscopic, transperitoneal approach. The peritoneum remains intact and the risk of visceral injuries is reduced. Hand-assistance results in a faster procedure and a significantly reduced operating time. The feasibility of this method has been demonstrated recently, but as to date there are no data available advocating the use of one technique above the other.

**Methods/design:**

The HARP-trial is a multi-centre randomised controlled, single-blind trial. The study compares the hand-assisted retroperitoneoscopic approach with standard laparoscopic donor nephrectomy. The objective is to determine the best approach for live donor nephrectomy to optimise donor's safety and comfort while reducing donation related costs.

**Discussion:**

This study will contribute to the evidence on any benefits of hand-assisted retroperitoneoscopic versus standard laparoscopic donor nephrectomy.

**Trial Registration:**

Dutch Trial Register NTR1433

## Background

Transplantation is the only treatment offering long-term benefit to patients with chronic kidney failure. As the number of patients suffering end stage renal disease (ESRD) increases, the recruitment of more kidney donors is important [1]. Live kidney donation is the most realistic option to reduce donor shortage on short- and long-term. Increasing the number of donors will decrease the number of patients on the waiting list and consequently reduce patient's mortality. Implementation of live donation offers the possibility to transplant before the kidney disease reaches the terminal phase, necessitating dialysis. Thus, this so called pre-emptive transplantation may prevent unnecessary surgical interventions to establish dialysis (including costs and mortality) and dialysis related complications. In the last decade the number of non-related live kidney donations is rising. Among these donors are family and friends of the recipient, and even anonymous donors; the ethical basis for live kidney donation is altering. The looser the connection between the donor and recipient is, the less clear the profit for the donor is.

Live donor nephrectomy is performed on healthy individuals who do not receive direct therapeutic benefit of the procedure themselves. In order to guarantee safety for the donors, it is important to optimise the surgical approach. Recently we demonstrated the benefit of laparoscopic nephrectomy (LDN) to the donor. However, this method is characterised by higher in-hospital costs, longer operating times and requires a well-trained surgeon [2]. The hand-assisted retroperitoneoscopic technique (HARP-technique) may be an alternative to a complete laparoscopic, transperitoneal approach. The peritoneum remains intact and the risk of visceral injuries is reduced. The hand-assistance results in a faster procedure and a significantly reduced operating time [3-7]. The feasibility of this method has been demonstrated recently, but as to date studies advocating the use of one technique above the other are lacking. This randomised controlled trial compares the hand-assisted retroperitoneal approach to the current standard, the transperitoneal laparoscopic technique, to define the most optimal approach.

We recently proved that laparoscopic kidney donation is beneficial for the donor. In comparison to minimally invasive open techniques, laparoscopic kidney donation is associated with a better quality of life, less pain, shorter in hospital stay and earlier return to work. This method is expensive for the hospital, has a long operating time and requires an experienced, well-trained, surgeon [2,8,9]. Other studies showed a possibly increased rate of life threatening complications, such as injuries to the intestines and bleeding [10,11]. A surgical approach that is easier to learn and applicable in the majority of donors (i.e. selection of donors is not required) with similar benefits as the transperitoneal laparoscopic approach is warranted.

The hand-assisted retroperitoneoscopic approach may be a viable alternative. With this method the surgeon inserts his hand to create a retroperitoneal space, which is thereafter insufflated with gas. The peritoneum stays intact and tactile sensation remains. The chance of a complication to the intestines is very small. Furthermore, this technique is easier and quicker to learn for the surgeon than the laparoscopic approach. There is no randomized controlled trial comparing both techniques for the effectiveness [3-6].

## Methods/Design

### Study objective

To determine the best approach for live donor nephrectomy i.e. to optimise donor's safety and comfort while reducing donation related costs.

### Study design

The HARP-trial is a multi-centre, randomised controlled, single-blind trial. We have stratified per centre. The study started on July 24th 2008 and the duration of the inclusion will be approximately 3 years. The study compares hand-assisted retroperitoneoscopic donor nephrectomy and standard laparoscopic donor nephrectomy. In total 190 live kidney donors will be included in the study. Approval of the medical ethical committee of both centres was obtained.

Randomisation will take place after endotracheal intubation, by means of telephonic consultation of the study coordinator. A computer generated randomisation list with hidden block size is made for each centre by the statistician. The donor and the physicians involved in the postoperative period are blinded to the surgical technique until one year after donor nephrectomy. The operating theatre is not accessible for people who do not join the operating team. An independent surgeon evaluates the donor on the outpatient clinic before operation. As the extraction incision is similar in both techniques, we did not attempt to cover the wounds with a standard pattern of bandages [12]. All donors fill out the questionnaires until one year after donation, the Short-form 36 (SF-36), Euroqol (EQ-5D), Visual Analogue Scale (VAS) and a questionnaire about work and homecare.

### Patient selection

All, properly Dutch speaking, live kidney donors who are medically capable of donating their left kidney can be included in the HARP-trial. Informed consent is mandatory. All types of live kidney donors can participate in the study, i.e. related, unrelated, altruistic and cross-over live kidney donors.

Exclusion criteria are a history of kidney surgery or adrenal gland surgery on the left side.

All potential donors are informed about the study at the outpatient clinic. For further information the patient can refer to the research fellow, transplant surgeon, or the independent physician. If a patient does not sign the informed consent form, the patient is not included in the study and therefore will be operated via the standard protocol. A live kidney donor can always withdraw his or her consent at anytime during the study.

### Hypothesis

The left-sided hand-assisted retroperitoneal approach will lead, with a similar or better quality of life, to fewer complications, and reduced operating times and costs.

### Study Questions

Primary Question: Does left-sided hand-assisted retroperitoneoscopic donor nephrectomy lead to a similar or better quality of life as compared to left-sided transperitoneal laparoscopic donor nephrectomy?

Secondary Question: Is the retroperitoneoscopic technique safer (conversions and complications) than the transperitoneal technique?

Other secondary endpoints: pain perception, return to work, operation time, cost-effectiveness from both a societal and health care perspectives (costs per quality adjusted life year).

### Pilot study

The Erasmus Medical Centre Rotterdam harbours one of the largest European live kidney donor transplantation programs. On a yearly basis 75 to a 100 laparoscopic donor nephrectomies are performed. Our strategy is to improve the results of live kidney donation by optimizing the surgical technique with decreased complication rates and costs. The infrastructure, raised in earlier studies, led to the formation of a multidisciplinary team, with a high standard of care and surgery.

In the previous study on live kidney donation running at our centre we compared the laparoscopic technique to the mini-incision muscle-splitting technique [2]. Laparoscopic donor nephrectomy resulted in early recovery, less fatigue and a better quality of life. However, the laparoscopic technique was more expensive from a hospital point of view and demanded more experience from the surgeon.

A pilot study with 60 live kidney donors showed the feasibility of the retroperitoneal hand-assisted approach [3]. Even in this small group operating time was significantly reduced. It seems feasible to expand the surgical armamentarium with this technique. However, we first have to demonstrate similar or better quality of life in comparison with the laparoscopic technique.

### Surgical intervention

Both procedures were performed with the donor placed in right-decubitus position. LDN was performed as described earlier [8]. Shortly, a 10-mm trocar was introduced under direct vision. The abdomen was insufflated carbon dioxide to 12 cm H_2_O pressure. A 30° video endoscope and 3 to 4 additional trocars were introduced. The colon was mobilized and displaced medially. Opening of the renal capsule and division of the perirenal fat was facilitated using an ultrasonic device (Ultracision, Ethicon, Cincinnati, USA). After identification and careful dissection of the ureter, the renal artery and the renal vein, a pfannenstiel incision was made. An endobag (Endocatch, US surgical, Norwalk, USA) was introduced into the abdomen. The ureter was clipped distally and divided. The renal artery and vein were divided using an endoscopic stapler and the kidney was placed in the endobag and extracted through the pfannenstiel incision.

In HARP we started with a 7-10 cm pfannenstiel incision [3]. After blunt dissection to create a retroperitoneal space, the Gelport (Applied Medical, Rancho Santa Margarita, California, USA) was inserted. Blunt introduction of the first trocar between the iliac crest and the handport was guided by the operator's hand inside the abdomen. CO_2 _was insufflated retroperitoneally to 12 cm H_2_O pressure. Two other 10-12 mm trocars, respectively just outside the midline inferior to the costal margin and in the flank, were inserted to create a triangular shape. For dissection the aforementioned ultrasonic device was used. Dissection of the kidney and renal vessels was similar to transperitoneal donor nephrectomy but with hand-assistance and from a slightly different angle. The kidney was removed manually.

### Outcome measures

Primary outcome: Physical functioning as a measure for quality of life one month after donor nephrectomy. This is one of the dimensions of the standardized SF-36 questionnaire. Physical functioning is measured by means of the complaints with daily physical activities, like walking stairs, carrying grocery bags, walking 500 meter, etc. The SF-36 is in our opinion a suitable parameter to measure post-operative recovery [13].

Secondary outcome: Direct costs (costs for the hospital). Other secondary endpoints: conversion to open surgery, complications, pain perception, work resumption, other dimensions of quality of life (SF-36), cost-effectiveness from hospital and health care perspective.

### Costs-effectiveness

In this effectiveness analysis the effect of the surgical procedure on quality of life of the donor and the costs for the hospital are the most important outcome measures. The donor is the central point of interest; therefore we chose quality of life as primary endpoint for the power calculation. Saving money, but with a worse quality of life for the donors is indeed not relevant.

### Power calculation

A difference of 7.5 point in physical functioning (SF-36) is a relevant difference. In international literature, a five point difference is the minimal clinically relevant difference [13]. In our previous study, reviewers thought this difference of five points was too small. Ten points is a big difference, but in our previous study this difference was observed after one month. A difference of 7.5 is in the middle of these data. Physical functioning is expressed on a scale of zero till hundred. Zero means a very limited function and hundred means an unrestrained function. With a measured standard deviation of 18.4 points (reference for left-sided kidney donation in the last five years), an alpha of 0.05, and a beta of 0.2, 95 donors have to be enrolled in both groups (Altman, Practical statistics for medical research, Chapman&Hall/CRC, 1991). Hereby we test two-sided, because the hand-assisted technique could be similar or even better than the laparoscopic technique. All data will be analysed according to the 'intention to treat' principle. Costs and effectiveness will be combined with the Euroqol 5-D to express the difference between both techniques in quality adjusted life years (QALYs).

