### Access to personal data

All personal data are coded into numbers (1 to 190). The coordinating investigator and the principle investigator are the only ones who have access to the coding system. All data are imported in a database, which is managed by the coordinating investigator. At the end of the trial all data are analysed together with the trial statistician.

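### The enrolment target equals the bare sample-size result, so the planned 80% power holds only if essentially every donor has a week-4 physical functioning score

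*Protocol article*

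**What the plan says.** All places are in the protocol article.

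- **Outcome measures** defines the primary outcome: "Physical functioning as a measure for quality of life one month after donor nephrectomy". It is one dimension of the SF-36, which donors complete themselves.
- **Power calculation** gives the inputs: "A difference of 7.5 point in physical functioning (SF-36) is a relevant difference"; "With a measured standard deviation of 18.4 points"; "an alpha of 0.05, and a beta of 0.2"; two-sided testing. It concludes that "95 donors have to be enrolled in both groups" and says that the analysis follows intention to treat.
- **Study design** sets the total: "In total 190 live kidney donors will be included in the study". **Access to personal data** uses the same number for the study codes: "All personal data are coded into numbers (1 to 190".
- **Patient selection** allows withdrawal: "A live kidney donor can always withdraw his or her consent at anytime during the study".
- **Treatment of participating live kidney donors** and its Table 1 schedule the SF-36 before surgery, at weeks 4, 6 and 8, and at months 3, 6 and 12. They also schedule an outpatient visit at four weeks.

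The article gives no expected rate of missing week-4 scores, no inflation of the sample size and no replacement of donors.

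**The concern.** The standard two-sample formula returns the number of participants per arm who contribute an outcome value. Here that number becomes the recruitment target unchanged. The target therefore has no reserve, although the outcome comes from a self-completed form four weeks after major surgery and consent can be withdrawn at any time. Intention to treat fixes the arm in which a donor is analysed. It does not supply a score for a donor who returned no form.

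The primary question is whether the hand-assisted technique gives similar or better quality of life, and the Costs-effectiveness section says that savings at the price of worse quality of life are of no interest. Lost power makes it more likely that a true 7.5-point difference goes undetected. The size of that loss depends on how many week-4 scores are missing.

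**Working it through.** **Inputs from the article:** difference 7.5; SD 18.4; two-sided alpha 0.05; beta 0.2; 95 per arm, 190 in total.

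**Assumptions made here:** missing rates of 5%, 10%, 15% and 20%; equal loss in both arms and unrelated to outcome, so that only power is affected; 18.4 is the unadjusted SD of the week-4 score; pre/post correlations of 0.2, 0.3 and 0.4.

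**1. Reproduce the stated figure (normal approximation).**

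n per arm = 2 × (1.96 + 0.8416)² × (18.4 / 7.5)² = 2 × 7.849 × 6.019 = 94.5, rounded up to 95. The total is 2 × 95 = 190.

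The figure reproduces, and 190 is exactly twice the bare result, so no allowance is hidden in the total.

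**2. Slack at 95 per arm.** By the normal approximation, power is 80.2% at 95 per arm and 79.8% at 94. By the noncentral t distribution it is 79.8% at 95, and 96 per arm are needed to pass 80%. There is practically no slack by either method. The rest uses the t-test throughout.

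**3. Power with missing week-4 scores, unadjusted t-test.** The noncentrality is 7.5 / (18.4 × √(2/n)) with 2n − 2 degrees of freedom. For n = 86 it is 7.5 / 2.806 = 2.673.

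| Assumed missing | Observed per arm | Power | Type II error |
|---|---|---|---|
| 0% | 95 | 79.8% | 20.2% |
| 5% | 90 | 77.6% | 22.4% |
| 10% | 86 | 75.7% | 24.3% |
| 15% | 81 | 73.2% | 26.8% |
| 20% | 76 | 70.4% | 29.6% |

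With 86 per arm, the difference detectable with 80% power is 7.9 points instead of 7.5.

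**4. Recovery by adjusting for the preoperative score.** The residual SD is 18.4 × √(1 − r²).

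| Assumed correlation r | Residual SD | Power at 86 per arm |
|---|---|---|
| 0.2 | 18.03 | 77.4% |
| 0.3 | 17.55 | 79.6% |
| 0.4 | 16.86 | 82.6% |

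At r = 0.3, adjustment about offsets a 10% loss. At 20% missing (76 per arm) even r = 0.4 gives 77.8%, so a large loss is not fully recovered.

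**The case against.** The case on the other side has real weight.

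- *The calculation contains no error.* This stands. The inputs lead to 95 and 190. A reader might infer a mistake in arithmetic, but the article's figures do not support that. What is missing is an allowance.
- *The shortfall is hypothetical.* This largely stands. A reader might infer that the trial is underpowered outright. The article gives no missing rate, so the loss is conditional. The right to withdraw is a general consent provision and says nothing about how often it will be used.
- *The design limits loss.* This stands. Randomisation takes place after intubation, so there is little room to drop out between allocation and surgery. The four-week clinic visit also coincides with the primary questionnaire. Neither feature guarantees that every form is returned.
- *The analysis may not be an unadjusted complete-case t-test.* This is fair. The article specifies only two-sided testing and intention to treat, and the model and the handling of missing data may sit in an analysis plan that is not shown. That bears on the size of the loss. The enrolment number and the power claim, however, are both stated in the article, and the power calculation uses no baseline information.
- *The effect is small.* This is true at plausible rates: about 2 percentage points at 5% missing. A shift from 7.5 to 7.9 points is small for a target that the article itself placed midway between 5 and 10.

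Because the primary question asks for similar or better quality of life, a reader might also carry the same loss over to a non-inferiority test at 7.5 points. The article states no non-inferiority margin, so that extension has no basis.

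**Conclusion.** The point holds as a minor issue with a sample-size assumption. The number of observed scores needed for about 80% power is also the entire enrolment, so the stated power depends on essentially complete week-4 data. On an unadjusted t-test the cost is about 2 percentage points of power at 5% missing (79.8% to 77.6%), about 4 at 10% (to 75.7%) and about 9 at 20% (to 70.4%). These sizes rest on assumed missing rates, on the article's SD of 18.4 and on loss unrelated to outcome. The design makes the lower end of that range more likely than the upper end. The preoperative SF-36 offers a way to regain much of the loss, to a degree that depends on a correlation the article does not report.

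**What to change.** 1. In the Power calculation section, make the claim conditional and use one method throughout. For example: *With a score at week 4 from all 190 donors, an unadjusted two-sided t-test has about 80% power (79.8%) to detect a difference of 7.5 points; if 10% of scores are missing, power is about 76%.* Replace the 10% by the rate that the sponsor considers plausible from its previous donor study.
2. Specify that the primary comparison adjusts for the preoperative SF-36 physical functioning score. Give the pre/post correlation from the previous donor data if it is available, since the recovery depends on it.

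The cost is a slightly less favourable power statement and one added covariate. The preoperative questionnaire is already scheduled in Table 1, so no extra donors, visits or forms are needed.

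### The primary claim is similar-or-better physical functioning, but the plan fixes a two-sided test for a 7.5-point difference with no margin or confidence-interval rule for similar

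*Protocol article*

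**What the plan says.** Four sections of the protocol article set out what the trial must show.

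- **Study Questions** (the main one of these): "Does left-sided hand-assisted retroperitoneoscopic donor nephrectomy lead to a similar or better quality of life as compared to left-sided transperitoneal laparoscopic donor nephrectomy".
- **Hypothesis**: "The left-sided hand-assisted retroperitoneal approach will lead, with a similar or better quality of life, to fewer complications, and reduced operating times and costs".
- **Pilot study**, on what must come before the technique is added to practice: "we first have to demonstrate similar or better quality of life in comparison with the laparoscopic technique".
- **Costs-effectiveness**: "Saving money, but with a worse quality of life for the donors is indeed not relevant".

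The primary outcome, under Outcome measures, is "Physical functioning as a measure for quality of life one month after donor nephrectomy", taken from the SF-36.

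The Power calculation section then fixes the statistical framework. It states: "A difference of 7.5 point in physical functioning (SF-36) is a relevant difference". It cites 5 points as the smallest clinically relevant difference in the literature and calls 10 points big. With SD 18.4, alpha 0.05 and beta 0.2 it arrives at 95 donors per group. On sidedness it says: "Hereby we test two-sided, because the hand-assisted technique could be similar or even better than the laparoscopic technique". Analysis is by intention to treat. No non-inferiority or equivalence margin appears, and nothing says how an interval would be judged to show similarity.

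**The concern.** To claim that HARP is similar or better, the trial must rule out that it is worse by an amount that matters. That takes a margin and a confidence limit that clears it. The plan has neither. Its 7.5 points serves as a difference to detect, not as a loss to exclude.

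The stated reason for two-sidedness adds to the problem. The two sides of such a test are better and worse. Similarity is neither, and failure to reject is not evidence of it.

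At stake is the primary conclusion. The donors are healthy people who gain no treatment benefit from the operation. The protocol's own logic is that gains in time, cost or complications count only if quality of life is not worse. Without a rule, a non-significant result could be taken as meeting that condition when the data still allow a relevant loss.

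**Working it through.** **Inputs**, all from Power calculation: difference 7.5, SD 18.4, two-sided alpha 0.05, power 0.80, 95 per group, literature minimum 5. No margin is stated, so 7.5 and 5 are used below as *assumed* margins because both figures stand in that section.

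**1. Reproduce the plan's figure.**
n = 2 × (z₀.₉₇₅ + z₀.₈₀)² × (SD/difference)² = 2 × (1.96 + 0.8416)² × (18.4/7.5)² = 2 × 7.849 × 6.019 = 94.5, rounded up to 95 per group. It reproduces. The one-sided 0.05 version gives 75, so the stated number is the two-sided calculation for detecting a difference.

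**2. Precision.**
SE = 18.4 × √(2/95) = 2.67. The half-width of the 95% interval is 1.96 × 2.67 = 5.23.

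**3. Results that are non-significant but do not exclude a 7.5-point loss.**
A deficit is non-significant if it is smaller than 5.23. The lower limit falls below -7.5 once the deficit exceeds 7.5 - 5.23 = 2.27. The problem range is therefore about 2.3 to 5.2 points.

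| Observed HARP minus LDN | 95% interval | p |
|---|---|---|
| 0 | -5.2 to 5.2 | 1.00 |
| -2 | -7.2 to 3.2 | 0.45 |
| -3 | -8.2 to 2.2 | 0.26 |
| -4 | -9.2 to 1.2 | 0.13 |
| -5 | -10.2 to 0.2 | 0.06 |

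Even an observed difference of zero does not exclude a 5-point loss.

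**4. Chance of a non-significant result when HARP is truly worse.**
1 - Φ(d/SE - 1.96), ignoring the negligible other tail:
- d = 5: 1 - Φ(1.873 - 1.96) = 53.5% (53.8% by the t-test).
- d = 7.5: 1 - Φ(2.809 - 1.96) = 19.8% (20.2% by the t-test).

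**5. What an interval rule would do with the same 95 per arm.**
The rule is that the lower limit of the two-sided 95% interval lies above minus the margin M. Power at true equality is Φ(M/SE - 1.96):
- M = 7.5: Φ(0.849) = 80.2%.
- M = 5: Φ(-0.087) = 46.5%. For 80% power, n = 2 × 7.849 × (18.4/5)² = 212.6, so 213 per arm (426 in total).

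The chance of declaring non-inferiority at M = 7.5 is 2.5% if the true difference is -7.5. If it is -5, the chance is Φ(2.5/2.67 - 1.96) = Φ(-1.02), about 15%.

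**6. Missing one-month questionnaires.**
The article states no allowance. Assuming 10% missing (about 86 per arm), SE = 2.81 and power at M = 7.5 is Φ(0.71), about 76%. Assuming 20% (76 per arm), SE = 2.98 and power is Φ(0.55), about 71%.

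**The case against.** The strongest reply is that the article nowhere says p > 0.05 will be read as similarity. A reader might infer that a non-significant p-value is the only route to *similar*. The text does not support that, since it does not exclude judging the confidence interval, and rules of interpretation are often left to an analysis plan, which is not shown here. Nor does the word superiority appear; that reading comes from the formula that reproduces 95. This part of the reply stands. It does not remove the point, because the article itself fixes the test, the role of 7.5 and a mistaken reason for two-sidedness, and these do not fit its primary question.

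A reader might also infer that the trial cannot support its own claim. That goes too far. At true equality the interval from 95 per arm would exclude a 7.5-point loss about 80% of the time. An observed deficit under about 2.3 points would be both non-significant and compatible with non-inferiority at 7.5. The rule is missing, not the data.

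A third inference is that a null result is likely because both techniques are endoscopic. The documents give no quality-of-life data comparing HARP with LDN, so this is conjecture.

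Finally, the Costs-effectiveness section already places savings below quality of life. It does so in principle, but gives no statistical criterion for *not worse*.

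**Conclusion.** The point holds as a mismatch between the primary claim and the stated test. The sample-size arithmetic is correct, but a two-sided test for a 7.5-point difference cannot establish similar-or-better physical functioning, and nothing in the article defines *similar*. The consequence is bounded. It bites for observed deficits of about 2.3 to 5.2 points, and a non-significant result arises about 53-54% of the time at a true 5-point deficit and 20% at 7.5. These figures assume SD 18.4, 95 evaluable donors per arm and a normal approximation.

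Because it governs how the primary result may be stated, it should be settled before analysis. The choice of margin remains open: 7.5 exceeds the 5 points that the protocol cites as the smallest relevant difference, so it cannot be taken over as a margin without justification.

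**What to change.** Before analysis:

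1. Restate the primary analysis as non-inferiority on one-month SF-36 physical functioning. Conclude *similar or better* only if the lower limit of the two-sided 95% interval for HARP minus LDN lies above minus a pre-specified margin that the sponsor justifies.
2. If that holds, test superiority from the same interval, which costs no alpha. Replace the sentence that explains two-sidedness.
3. State that p > 0.05 alone will not be reported as similarity.
4. If the margin is 7.5, also report the lower limit against -5 and say that a 5-point deficit may not be excluded.
5. Keep intention to treat as primary. A supporting analysis should not drop donors because they were converted: conversion happens after randomisation and is itself a listed endpoint, so dropping them could flatter the technique that converts more.
6. Report and interpret complications whatever the non-inferiority result. The protocol asks the safety question separately.

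**Cost.** At a margin of 7.5 this changes wording only: 95 per arm gives about 80% power with complete data, and less with missing questionnaires. At a margin of 5 it means either about 213 per arm or accepting about 47% power.
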